### Trial design

PROPENSIX is a multicenter, prospective, double-blinded, randomized, placebo-controlled superiority trial using a medical device. The seven French study centers involved are specialized in pediatric rehabilitation. Both parents/children and physicians/therapists are blinded regarding the type of sleeve (active or placebo) used during the whole duration of the trial. Un-blinding will be performed for statistical analysis since it is needed for safety outcome comparison between the groups. Primary aim statistical analysis will be also un-blinded as adherence level is mandatory for future intention-to-treat and per-protocol statistical analysis.

Enrollment into the PROPENSIX study started in December 2012 and has been completed since September 2020. The clinical phase of the study was completed in April 2021. The coding process (neurologic exams, AHA, QUEST, and quality of life tests) and data handling are ongoing until the end of 2022.

Subjects are enrolled by the investigator of each study center. The randomization is centralized. The randomization sequence was provided by an independent statistician (who did not take part in assessing the patients at any point in the study) using computer-generated random numbers structured in blocks. The block size information is not specified in the protocol to ensure that investigators are not able to anticipate treatment arm assignment. The randomization ratio is 1:1. The randomization list is maintained by the sponsor. It has been communicated to the splint manufacturer, Medical Z^®^, ensuring a randomized allocation of the sleeves to each included child, on condition of anonymity.

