### Population

#### Patient’s eligibility

The inclusion criteria are children with ante-natal or peri-natal hemiplegic cerebral palsy, aged 5 to 10, having social insurance, written informed consent. The exclusion criteria are allergy to Lycra^®^, contra-indication to pressure therapy (e.g., skin lesions, allergic contact dermatitis), behavior or speech troubles, treatment with Botulinum Neurotoxin on the involved arm within the preceding 4 months, children under tutorship or curatorship, and predictable lack of compliance.

Patients may be discontinued from this trial at any time, firstly for voluntary discontinuation. Other specific reasons for discontinuing a patient are the administration of Botulinum Neurotoxin on the involved arm during the study and/or compliance under 80%. Any discontinuation is referred as soon as possible to the principal investigator. Data regarding the discontinued patients will be analyzed in the intention-to-treat analysis.

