##### Daily activities

After enrollment, the child is asked to wear the sleeve (active or placebo) at least 3 h a day, every day, for 6 months. The sleeve has to be worn during usual daily activities, especially in activities involving bimanual performances, and during rehabilitation sessions. Each patient’s therapists (physiotherapists and occupational therapists) are informed of the child enrollment in a trial and asked to follow instructions of harmonization for rehabilitation, but there is no major modification of the usual rehabilitation care.

Written general recommendations are provided to guide rehabilitation:
Stimulation of proprioceptive function: analytic proprioception stimulation, ground bearing and weight-bearing transfers, installation quality and symmetry, mirror feedback, and dynamic proprioception stimulation (opposition and pushing games, moving of heavy objects).Stimulation of active mobility, on proximal and distal levels of the hemiplegic side, with static shoulder and arm, hand aiming, approach, and grip and release exercises.Stimulation of bimanual coordination during daily activities, developing assisting hand capacities, and passing from one hand to the other.

Additional personalized recommendations are added, regarding the child’s state of development and actual capacities of the upper extremity.

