**Fig. 2 Fig2:**
[figure not shown]
Experimental design. AHA, Assisting Hand Assessment

After giving their consent, participants are recruited and randomized during the inclusion visit (V1) which happens 1 month before the beginning of the intervention. The occupational therapist or investigator, specifically formed, takes precise measurements of the child’s arm, following the manufacturer’s instructions. The investigator sends the measurement data to Medical Z®, so that the confection of the sleeve can begin by the manufacturer according to randomization list (active sleeve or placebo sleeve), on condition of anonymity. The sleeve will be delivered by the manufacturer to the study center within 15 + 3 days. The investigator delivers the tailor-made sleeve (active or placebo) to the child and parents during the baseline visit (V2), with oral and written instructions regarding its utilization and care. In addition, the investigator edits the recommendations for rehabilitation harmonization, destinated to therapists involved in the child’s usual care. The sleeve is reclaimed at the end of the study. Involved therapists, investigators, patients, and their parents are blinded regarding the type of sleeve (active or placebo) received by the child according to randomization.

Outcomes evaluation occurs 1 month after inclusion, during the baseline visit (V2), and at the end of the intervention, after 6 months of daily wear of the Lycra^®^ sleeve, and during the final visit (V4). Baseline and final testing are realized without wearing the splint. AHA, the primary outcome, is assessed by a certified occupational therapist. QUEST is assessed by the same experienced occupational therapist, following the QUEST manual [35]. Neuro-orthopedic examination is conducted by the investigator following the report form of the study. SEP are recorded by an experienced neurophysiology technician. PedsQL™ 3.0 CP Module questionnaire is completed by the child’s parents. Anthropometric measurements occur at V2, V3, and V4. Compliance is monitored in a diary, specifically developed for the study purpose. Compliance data are checked at V3 and V4. Adverse reactions are recorded as well during V3 and V4.

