### Statistical analysis

The variation of the Assisting Hand Assessment (AHA) from baseline to 6 months is the primary outcome. Secondary outcomes are the Quality of Upper Extremity Skill Test (QUEST), the Pediatric Quality of Life Inventory 3.0 Cerebral Palsy module (PedsQL™ 3.0 CP Module, Parents Report), SEP parameters (N13-N20 interval, P14-N20 interval, ratios of delay conduction, amplitudes of N20-P27 and amplitude ratio), neuro-orthopedic examination (results of the second examination, 6 months later, scored in comparison with the first examination on a 0 to 3 scale: 0 = normal range of motion, 1 = lower anomaly, 2 = stable anomaly, 3 higher anomaly).

Statistical analyses will be independently performed by the Biostatistics Department of Lille University. Data will be analyzed using the SAS software (SAS Institute Inc, Cary, NC, USA), and all statistical tests will be performed with a 2-tailed alpha risk of 0.05. Baseline characteristics will be described for each group, categorical variables will be expressed as frequencies and percentages, and quantitative variables will be expressed as means and standard deviation in case of normal distribution or medians (interquartile range) otherwise normality of distributions will be assessed graphically and by using the Shapiro-Wilk test. No formal statistical comparisons of baseline characteristics will be done; clinical importance of any imbalance will be noted. For the primary analysis, both analyses (ITT and per-protocol) will be considered to support the conclusion of non-inferiority [45]. ITT population includes all randomized participants based on their original group of randomization. Per-protocol population includes all randomized patients excluding those with major protocol violations: patients who do not complete the rehabilitation procedure allocated after randomization, discontinuation for lack of compliance or personal reasons, adverse reaction. For the secondary objectives, we will use only the ITT population.

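### The per-protocol set is built on a rehabilitation procedure the trial does not allocate, reaches sleeve wear only through discontinuation, and excludes for adverse reaction

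*Protocol article*

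**What the plan says.** All references are to the protocol article.

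- **Statistical analysis.** "Per-protocol population includes all randomized patients excluding those with major protocol violations". The violations listed are "patients who do not complete the rehabilitation procedure allocated after randomization, discontinuation for lack of compliance or personal reasons, adverse reaction". ITT and per-protocol results are both to be considered for the primary conclusion; secondary objectives use ITT only.
- **Trial design** and **Study visits.** The randomisation list determines which sleeve, active or placebo, the manufacturer makes for each child.
- **Daily activities.** The sleeve is to be worn "at least 3 h a day, every day, for 6 months". The child's therapists are "asked to follow instructions of harmonization for rehabilitation, but there is no major modification of the usual rehabilitation care".
- **Level of adherence.** Adherence is the percentage of days on which wear reaches 3 h, over the span from start to end of wearing, taken from a daily diary.
- **Patient's eligibility.** "Patients may be discontinued from this trial at any time". The specific reasons given are botulinum toxin on the involved arm during the study and compliance under 80%.
- **Trial design.** Un-blinding for the primary analysis is justified on the ground that "adherence level is mandatory for future intention-to-treat and per-protocol statistical analysis".

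**The concern.** A per-protocol set is meant to hold children who received the randomised treatment broadly as specified. Here the treatment is the sleeve, and the protocol has a measure of its use and a threshold. The definition of the set cites neither. It starts from a rehabilitation procedure that no arm is allocated, uses compliance only when it led to discontinuation, and counts an adverse reaction as a protocol violation although a reaction may be a consequence of the device.

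Two things are at stake. The set can keep children who hardly used the sleeve, and it can drop children for an event that may be related to arm. Membership is also open to interpretation at a stage when the analysis is planned to be un-blinded, so unclear cases could be settled with allocation known.

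**Working it through.** The point concerns a definition, so the check is to apply it to particular cases.

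**What is allocated.** Trial design and Study visits allocate the sleeve. Daily activities keeps rehabilitation as usual care, with written harmonisation advice for every child. Taken literally, the first exclusion either selects nobody or removes children who missed usual therapy, which is not the randomised treatment.

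**Four cases.**

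| Child | Under the definition as written | Under a wear-based definition |
|---|---|---|
| Wear below 80% of days, not discontinued, seen at V4 | Not clearly excluded | Out |
| Wear at or above 80%, had a reaction, completed V4 | Out if any reaction counts; in if only discontinuation for a reaction counts | In |
| Stopped late because of a reaction, with 80% of scheduled days already reached, AHA obtained | Out on either reading | In |
| Botulinum toxin on the involved arm, not discontinued | Not named | Depends on how the two sections are reconciled |

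The third case can occur. Six months is about 182.6 days, and 0.80 × 182.6 = 146 days. A child who wore the sleeve for 3 h every day could stop about 182.6 − 146 = 36 days early and still meet the figure.

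**The denominator.** Adherence is measured between the start and end dates of wearing. If the end date is the day the child stopped, a child who wore the sleeve daily for 3 months and then gave up scores 3/3 = 100%. Over the scheduled V2 to V4 period the same child scores 3/6 = 50%.

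**Dependence on arm.** The Lycra sleeves section gives 15 to 25 mmHg for the active sleeve and under 5 mmHg for placebo. Safety outcome lists compression events such as swelling, arm pain and tightness. A difference between arms is plausible, but no rates are given.

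**Scale.** The claim rests on no stated figure, but the sample size section shows what a smaller set would cost.

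- Difference: 1.8 − 0.72 = 1.08 logit; SD 2.
- Unadjusted n per arm (normal approximation): 2 × [2 × (1.960 + 0.842)/1.08]² = 53.8, against 53 stated.
- Adjusted for a correlation of 0.4: 53 × (1 − 0.16) = 44.5, against 45 stated.
- With 10% non-analyzable: 45/0.9 = 50 per arm, as stated.

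The plan's figures reproduce to within one patient. With adjusted SD 2 × √0.84 = 1.83, power is 84% at 50 per arm, 80% at 45, 75% at 40, 69% at 35 and 63% at 30. The document gives no expected per-protocol size, so these only illustrate the cost.

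**The case against.** The best defence is that the definition is loosely worded but workable.

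- **Wear is not ignored.** Discontinuation for lack of compliance is one of the exclusions. Patient's eligibility attaches 80% to compliance, and the adherence section defines it by days with 3 h of wear. A reader might infer that the set disregards sleeve wear; the document does not support that. What remains is that the link is indirect, is not cross-referenced, and fails for a child who was not discontinued.
- **The rehabilitation phrase may stand for the sleeve therapy.** On that reading a child discontinued for botulinum toxin is out as a non-completer. This is possible, but the words do not say it, and a child given the toxin and kept in the trial is still not covered.
- **Adverse reaction may mean discontinuation because of one.** This is a natural reading of the list. It narrows the problem, but selection would still be on an event that could differ by arm.
- **Selective loss from the active arm is not shown.** The placebo is also a worn sleeve, so skin events could occur in both arms, and the Discussion expects adverse effects to be minor. This stands: bias is possible, not demonstrated.
- **A wear threshold is also a post-randomisation selection.** If compression is uncomfortable, active-arm children may fail it more often. This stands too, and it is why the analysis should remain supportive.
- **Operational detail may sit in an unseen analysis plan.** That is fair for visit windows and similar matters. It does not repair criteria that the article states and that conflict with its other sections.

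**Conclusion.** The concern holds in limited form. As written, the per-protocol set refers to a procedure this trial does not allocate, does not apply the adherence measure that Trial design calls mandatory for it, and excludes on an event that may depend on arm. It is an unclear and possibly biased approximation to the effect of wearing the sleeve. To say that it cannot estimate that effect at all would go too far.

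The consequence is confined to the per-protocol half of the primary analysis. ITT runs alongside it and keeps discontinued children, and secondary objectives use ITT only. That half still matters, because both analyses are to be weighed in the primary conclusion.

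The size cannot be derived from the document. One might reckon that 10% low wearers with no benefit would dilute the assumed difference to 0.9 × 1.08 = 0.97 logit, or that a 10% reaction rate would remove about 5 active-arm children. Both 10% rates are assumptions, as is zero benefit below the threshold, so neither result is a finding. The conclusion rests on the wording alone, plus the plausible but unquantified premise that compression-related reactions could differ between the two pressures.

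**What to change.** Redefine the per-protocol set before the analysis is un-blinded:

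1. Base it on the allocated sleeve and remove the reference to an allocated rehabilitation procedure.
2. Require the protocol's own adherence measure, days with at least 3 h of wear, to reach the 80% figure already in Patient's eligibility. Use the scheduled V2 to V4 period as denominator and apply the rule whether or not the child was formally discontinued.
3. Remove adverse reaction as an exclusion in itself. Such a child leaves the set only by failing the wear criterion or lacking AHA.
4. Reconcile the botulinum toxin criterion between Patient's eligibility and Statistical analysis, so that the status of a child who received it and was not discontinued is explicit.
5. Keep the analysis supportive of ITT, since a wear-based set is still selected after randomisation.

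The cost is a change of wording. Daily wear is in the diary, compliance is checked at V3 and V4, and AHA is scheduled at V2 and V4. The set may be somewhat smaller, with the loss of precision illustrated in the power figures above.

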#### Primary outcome

The variation of the Assisting Hand Assessment (AHA) from baseline to 6 months will be compared between the two treatment groups using the constrained longitudinal data analysis (cLDA) model proposed by Liang and Zeger [46] including the same fixed and random effects as in the primary efficacy model. This model will be used in view of the potential advantages of the cLDA compared to the conventional longitudinal analysis of covariance (ANCOVA) model [47]. In the cLDA, both the baseline and post-baseline values will be modeled as dependent variables using a linear mixed model (using an unstructured covariance pattern model), and the true baseline means will be constrained to be the same for the 2 treatment groups. The between-group mean differences in 6-months change in AHA will be estimated by the time-by-arm interaction as treatment effect size. In absence of missing data, the cLDA model provides the same point estimates of treatment differences than the ANCOVA model. Nevertheless, cLDA presents two main advantages with regard to the ANCOVA model: first, the estimated variance from the ANCOVA model is always greater than or equal to that from the cLDA model and consequently cLDA model provides more appropriate confidence interval of estimates. Second, if there are missing values, the cLDA model allows to provide unbiased estimates of the treatment effect under the MAR (missing at random) assumption, which is not the case for the ANCOVA model. If the assumption of normality of model residuals is not satisfied (even after log-transformation), non-parametric analysis will be used; absolute changes between baseline and 24 h will be calculated and compared between the 2 treatments groups using non-parametric analysis of covariance adjusted for baseline values [48].

Missing data (whatever the reason) will be handling using the multiple imputation procedure [49,50]. Imputation procedure will be performed using main baseline characteristics and treatment group under missing at the random assumption by using regression switching approach (chained equation with *m* = 20 imputations) with a predictive mean matching method for continuous variables, logistic regression models (binary, ordinal or polynomial) for categorical variables. Imputation procedure will be performed using the baseline characteristics and allocated group. Treatment effect estimates obtained in multiple imputed data sets will be combined using the Rubin’s rules [51]. Complete case analysis will be performed as a sensitivity analysis [52].

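### For discontinued children without a 6-month AHA, the intention-to-treat imputation uses only baseline and arm under MAR, and no stated analysis would show an overstated effect

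*Protocol article*

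**What the plan says.** Patient's eligibility: "Patients may be discontinued from this trial at any time". Besides voluntary withdrawal, the named reasons are "the administration of Botulinum Neurotoxin on the involved arm during the study and/or compliance under 80" per cent. The same section adds: "Data regarding the discontinued patients will be analyzed in the intention-to-treat analysis".

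Statistical analysis: "ITT population includes all randomized participants based on their original group of randomization". The per-protocol set leaves out, among others, children discontinued for lack of compliance, personal reasons or an adverse reaction.

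Primary outcome, under Statistical analysis: "Missing data (whatever the reason) will be handling using the multiple imputation procedure", assuming MAR with 20 imputations. The predictors are given twice, the second time as "Imputation procedure will be performed using the baseline characteristics and allocated group". Adherence, discontinuation status and toxin use during the study are not among them. The one sensitivity analysis named is: "Complete case analysis will be performed as a sensitivity analysis".

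Table 2 (Study visits) schedules AHA at V2 and V4 only, and compliance evaluation at V3 and V4. The adherence section says that daily hours of wear, and the reason when wear falls below 3 hours, are kept in a diary.

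**The concern.** A child who leaves before V4 has no post-baseline AHA. The model then has only that child's baseline data and arm to work from, and it predicts the 6-month value from children in the same arm whose V4 was observed. For an active-arm child who stopped wearing the sleeve, this amounts to assuming the benefit continued. The constrained longitudinal model does not help, because with two AHA time points it has no interim value to draw on.

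MAR given baseline and arm is hard to defend here. Low compliance arises after randomisation, and the Introduction attributes the hoped-for benefit to wearing the sleeve during bimanual activity. The Trial design section itself says adherence level is needed for both the ITT and per-protocol analyses, yet the imputation model leaves it out.

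The planned checks share the limitation. Complete case drops the children concerned, and per-protocol excludes most of them by definition. The three results would tend to agree, and that agreement could be mistaken for robustness. At stake are the size and meaning of the primary estimate as an effect in all randomised children.

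**Working it through.** **Inputs from the article (Sample size estimates).** Placebo mean 1.8 logit, active mean 0.72, so a difference of 1.08 in absolute size; SD 2; baseline correlation 0.4; two-sided alpha 5%; power 80%; 10% non-analysable data.

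**Reproducing the plan's figures.**
- Unadjusted: 2 × [2 × (1.960 + 0.842) / 1.08]² = 53.8, so 54 per arm against the stated 53.
- Baseline-adjusted: 53 × (1 − 0.4²) = 53 × 0.84 = 44.5, so 45.
- With 10% non-analysable: 45 / 0.90 = 50 per arm.

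The 1.08 logit is therefore the effect the trial was sized on.

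**Assumptions the article does not supply.** Let s be the share of active-arm children who stop and have no V4 AHA, and λ the share of the effect they keep.
- Effect in all randomised children: 1.08 × [(1 − s) + s × λ].
- Target of imputation from baseline and arm: 1.08, the effect in those who remain.
- Overstatement: 1.08 divided by the first line, minus 1.

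| s | λ | Effect in all randomised | Overstatement |
|---|---|---|---|
| 10% | 0.5 | 1.08 × 0.95 = 1.026 | 5% |
| 10% | 0 | 1.08 × 0.90 = 0.972 | 11% |
| 20% | 0.5 | 1.08 × 0.90 = 0.972 | 11% |
| 20% | 0 | 1.08 × 0.80 = 0.864 | 25% |

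**Relative to precision.** With 45 per arm the standard error is about 2 × √0.84 × √(2/45) = 0.39 logit. The gap is 0.054 to 0.108 logit at s = 10%, or 0.14 to 0.28 standard errors. It is 0.108 to 0.216 logit at s = 20%, or 0.28 to 0.56 standard errors.

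**Simulation of the planned procedure.** 50 per arm, predictive mean matching on baseline and arm, 20 imputations, Rubin's rules, 600 runs per scenario, the same stopping share in both arms. Mean estimates:

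| s | λ | Full follow-up | Planned imputation | Complete case |
|---|---|---|---|---|
| 10% | 0.5 | 1.04 | 1.08 | 1.09 |
| 10% | 0 | 0.99 | 1.09 | 1.10 |
| 20% | 0.5 | 0.96 | 1.04 | 1.06 |
| 20% | 0 | 0.89 | 1.09 | 1.11 |

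Imputation and complete case give nearly the same answer in every row, so comparing them would not expose the gap to full follow-up. Unequal stopping between arms is not needed to produce it.

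**Strict null.** With no effect in anyone and s = 20%, rejection was 6.0% with imputation and 5.7% with full data, which is within simulation error.

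**The case against.** The strongest reply is that the premise is conditional. The article never says V4 AHA is missing after discontinuation. It says the children's data enter ITT, and Ethical considerations says the consent form asks about use of data after withdrawal. Discontinuation is permitted, not automatic. Compliance is evaluated only at V3 and V4, so a child found below 80% at V4 is already at the visit where AHA is taken. Low compliers who stay are observed and feed the imputation model.

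The magnitude is also assumed. The 10% in the sample-size section is an overall rate of non-analysable data, not an active-arm stopping rate. Keeping none of the effect is the extreme case: adherence is the share of days with at least 3 hours of wear, so a child just under 80% has worn the sleeve a good deal. The simulation shows how the stated procedure behaves, but it cannot supply s or λ. The Discussion expects good tolerance, and poorer outcomes among placebo-arm stoppers could offset part of the gap. Finally, an unseen analysis plan might hold further sensitivity analyses.

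Most of this stands and limits the point. A reader might infer that the ITT estimate simply becomes the effect in compliers, that every discontinuation inflates it, or that the trial is exposed to false positives. The documents support none of these. The remaining children are mostly, not only, compliers; the direction for toxin-treated children is undetermined; and the null rejection rate is essentially unchanged.

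One thing is not answered. The article positively fixes the predictors, the MAR assumption and one sensitivity analysis, and nothing it describes would detect a departure from MAR related to stopping.

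**Conclusion.** The point holds in conditional form. For a discontinued child without a V4 AHA, the stated method assigns an outcome typical of same-arm children who remained, and neither complete case nor per-protocol can show whether that is wrong. If low-compliance stoppers in the active arm gain less, the ITT effect is overstated: by about 5% to 11% with 10% of the arm stopped and missing, and by about 11% to 25% with 20%. Each range runs from half the effect kept to none kept.

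These figures rest on assumed stopping shares and retained effects, and on placebo-arm stoppers behaving like other placebo children. Where V4 AHA was obtained and used, the problem disappears for that child. It is a should-level improvement to the primary analysis and does not show that the trial's conclusion would be wrong.

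**What to change.** 1. State that every V4 AHA obtained enters the ITT analysis, whatever the child's compliance, discontinuation or toxin use. The clinical phase ended in April 2021, so this governs use of data already collected and cannot add visits.
2. Add diary adherence to the imputation model, letting its relation to AHA differ by arm. Add discontinuation status only if some discontinued children have an observed V4 AHA; otherwise its coefficient cannot be estimated. Do not rely on 6-month QUEST, which is taken at the same visit and will usually be missing with AHA.
3. Keep complete case, and add a sensitivity analysis that departs from MAR: placebo-reference imputation for discontinued active-arm children, a delta tipping-point analysis, or both. If few stoppers have a V4 AHA, this step carries most of the remedy.

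The cost is wording and programming, a slightly wider interval and possibly a smaller reported effect. The article says coding and data handling run to the end of 2022, so on that timetable the change can precede the analysis. No change to any clinical discontinuation rule is proposed.
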